#### Statistical analysis plan

The primary analysis will be by the intention-to-treat principle and will include all randomised patients on whom an outcome is available [20]. All tests will be two-sided, and all analyses will be adjusted for the minimisation variables [21-24]. The primary outcome will be analysed using a time-to-event regression model, which will include mortality as a competing risk. The full statistical analysis plan for the IPC-PLUS trial will be written and ratified by the Trial Steering Committee prior to data unblinding, and will be published in a separate document.

#### Interim analysis

One interim analysis will be carried out after 100 patients are randomised in order to test for efficacy. The O’Brien-Fleming stopping rule will be used, which requires a *P* value of <0.005 for the primary endpoint in order to stop the trial early [25]. If the trial is not stopped at the interim analysis, the O’Brien-Fleming rule requires a *P* value of <0.048 at the final analysis in order to declare a statistically significant difference in the primary endpoint. The results of the interim analysis will be presented to the Independent Data Monitoring Committee, who will make a recommendation to the Trial Steering Committee as to whether the trial should stop early. This recommendation will also take into consideration other sources of evidence aside from the primary endpoint, such as secondary outcomes and safety data.

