**Methods/Design:**

IPC-PLUS is a patient-blind, multicentre randomised controlled trial (RCT) comparing the combination of talc with an IPC to the use of an IPC alone for inducing pleurodesis in MPEs. The primary outcome is successful pleurodesis at five weeks post-randomisation. This study will recruit 154 patients, with an interim analysis for efficacy after 100 patients, and aims to help to define the future gold standard for outpatient management of patients with symptomatic MPEs.

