### Sample size and power calculation

Talc pleurodesis alone has been shown to be up to 90% efficacious in trial conditions [3], and we expect the combination of talc and IPC to be at least as effective as talc alone. IPCs used alone have a more variable range for pleurodesis efficacy, but suggest an average rate of around 50%.

Therefore, in order to detect a 25% difference in pleurodesis success at five weeks (using conservative estimates of 60% IPC alone versus 85% IPC and talc) with 90% power, a 5% significance level and 5% loss to follow-up, we would require 154 patients (77 in each arm). An interim analysis for efficacy will take place after 100 patients are randomised.

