### End of trial

The trial will cease recruitment once the target of 154 randomised patients has been met, or if the Trial Steering Committee feels the interim analysis after 100 patients justifies early cessation. The provisional end of trial date will therefore be 10 weeks after the randomisation of the final trial patient. At the end of each patient’s follow-up period they will be stratified as ‘alive’ or ‘dead’, and survival data collated. Further information regarding participants’ health status and survival may be obtained by accessing the NHS central register. This will require consent to be given separate to trial involvement. Those who still have an IPC *in situ* will have their care devolved to the appropriate local services.

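### The limits P<0.005 and P<0.048 are the O'Brien-Fleming values for a look at half the information, not for a look after 100 of 154 patients; error control holds, but early stopping is harder than the named rule makes it

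*Protocol article*

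**What the plan says.** Under Interim analysis, the protocol article states: "One interim analysis will be carried out after 100 patients are randomised in order to test for efficacy". It names the O'Brien-Fleming stopping rule and says that the rule requires a *P* "value of <0.005 for the primary endpoint in order to stop the trial early" and, if the trial continues, a *P* "value of <0.048 at the final analysis in order to declare a statistically significant difference in the primary endpoint".

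The total is fixed elsewhere. Sample size and power calculation gives it as "with 90% power, a 5% significance level and 5% loss to follow-up, we would require 154 patients (77 in each arm"), for success rates stated as "using conservative estimates of 60% IPC alone versus 85% IPC and talc". End of trial adds: "The trial will cease recruitment once the target of 154 randomised patients has been met". The Statistical analysis plan section makes all tests two-sided and specifies a time-to-event regression model for the primary outcome, with mortality as a competing risk.

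The article gives no information fraction, spending function or other basis for the two limits.

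**The concern.** O'Brien-Fleming limits depend on when the look takes place. The earlier the look, the stricter the interim limit and the closer the final limit stays to 0.05. The values 0.005 and 0.048 are the familiar ones for two equally spaced looks, which would put the interim at half the information. The planned look is at 100/154 = 65% of patients. The article therefore names a rule, fixes a timing, and states limits that the rule does not give at that timing.

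These two numbers are the statistical criteria for recommending early stopping and for declaring the primary endpoint significant. This is not detail left to a separate analysis plan: the rule, the timing and both limits are already written down. An analysis plan that follows the article inherits the mismatch, and one that corrects it contradicts the article.

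**Working it through.** **Inputs.** Interim after 100 randomised; total 154; overall two-sided alpha 0.05; 60% v 85% success; 90% power; 5% loss to follow-up (Interim analysis; Sample size and power calculation; Statistical analysis plan).

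**Sample size.** A two-proportion formula with continuity correction gives 73 per arm. Allowing for 5% loss, 73/0.95 = 76.8, so 77 per arm and 154 in total. The stated size is reproduced.

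**Model for the limits.** Z1 and Z2 are bivariate normal with correlation √t, where t is the information fraction at the look.
- Classical O'Brien-Fleming: c1 = c/√t and c2 = c, with c solving 1 − P(|Z1|<c1, |Z2|<c2) = 0.05.
- Lan-DeMets O'Brien-Fleming-type spending: two-sided alpha spent at the look = 4[1 − Φ(z/√t)], with z = Φ⁻¹(1 − 0.0125); c2 then solves for the remaining alpha.

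**Limits (two-sided P, interim / final).**

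| t | Classical | Lan-DeMets | Overall alpha of the stated pair |
|---|---|---|---|
| 0.50 | 0.0052 / 0.0480 | 0.0031 / 0.0490 | 0.0499 |
| 0.51 | 0.0056 / 0.0478 | 0.0034 / 0.0489 | 0.0499 |
| 0.55 | 0.0075 / 0.0472 | 0.0050 / 0.0484 | 0.0496 |
| 0.58 | 0.0090 / 0.0467 | 0.0065 / 0.0479 | 0.0494 |
| 100/154 = 0.649 | 0.0131 / 0.0455 | 0.0108 / 0.0466 | 0.0490 |

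The stated pair is reproduced by the classical rule at t = 0.50. At t = 0.649 the classical critical values are 2.482 and 2.000, and the Lan-DeMets values 2.548 and 1.990.

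**How far information may fall short of 65%.** Assume 2.5 to 9.4 randomisations a month: 60 over the 24 months to July 2014 is 2.5, and the remaining 94 over the 10 months to May 2015 is 9.4. If data are cut when patient 100 is randomised, patients with complete 5-week data are about 58-63% of 154, and with complete 10-week data about 51-61%.

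**Chance of crossing at the interim under 60% v 85%.** Take 50 × 0.95 = 47.5 evaluable per arm and an unadjusted pooled two-proportion test.
- Pooled rate 0.725; SE0 = √(2 × 0.725 × 0.275/47.5) = 0.0916.
- SE1 = √((0.60 × 0.40 + 0.85 × 0.15)/47.5) = 0.0880.
- Probability = Φ((0.25 − z × SE0)/SE1), with z the critical value.
- P<0.005 (z = 2.807): Φ(−0.08) = 47%.
- P<0.0108 (z = 2.549): Φ(0.19) = 57%.
- P<0.0131 (z = 2.481): Φ(0.26) = 60%.

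The loss is 10 to 13 points. A second basis uses a drift of 1.960 + 1.282 = 3.242, set for 90% fixed-design power, so the interim mean is 3.242 × √0.649 = 2.612. It gives about 42%, 53% and 55%.

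**Overall power on that drift at t = 0.649.** 0.898 for the stated pair, 0.897 for Lan-DeMets, 0.896 for classical.

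**Mixed corrections at t = 0.649.** Correcting only the interim limit and keeping 0.048 gives overall alpha 0.0513 (Lan-DeMets) or 0.0523 (classical). Keeping 0.005 at the interim, the final limit that uses the full 0.05 is 0.0490.

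**The case against.** A reader might infer that the mismatch inflates the false-positive rate, or that 0.048 is too lenient. The figures do not support either. The pair is fixed in advance, is unambiguous, and has an overall alpha of 0.0490 at 65%. Once 0.005 is used at the look, 0.048 is on the strict side of the full-alpha limit of 0.0490. A final P between about 0.0466 and 0.048 would fall outside the named rule, but declaring it significant breaches no error rate under the stated pair. Nor is overall power lost. It is therefore too strong to call both thresholds simply wrong: what fails is their attribution to O'Brien-Fleming at this timing.

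The second objection is that 65% is a share of patients. Information in a competing-risk time-to-event analysis follows events, and the look is triggered by randomisation rather than by completed follow-up. This stands in part. Lower information narrows the gap, and 65% is near the top of the plausible range. The classical limits come near the stated pair only around 51%. Lan-DeMets spending at about 55% happens to give 0.0050 and 0.0484, but the article states neither that fraction nor a spending function.

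Third, the crossing probabilities do not use the planned adjusted model, so they are illustrative. Crossing would not stop the trial by itself either: the data monitoring committee recommends, weighing secondary outcomes and safety too, and the Trial Steering Committee decides. Both points stand. A strict interim limit is also a defensible choice, but the article presents this one as what O'Brien-Fleming requires.

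**Conclusion.** The point holds as a mismatch between the named rule, its stated timing and its stated limits. On a patient-count basis the O'Brien-Fleming limits at the look are about 0.013 and 0.0455 (classical) or 0.011 and 0.047 (Lan-DeMets), against 0.005 and 0.048 as written. At 58% information the classical limits are still about 0.009 and 0.047.

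The consequence is modest. Type I error stays below 5% and overall power is about 0.90 under any of the three pairs. What is lost is roughly 10 to 13 percentage points of the chance of crossing at 100 patients if the design rates hold. That size assumes 65% information and a simple two-proportion comparison; it shrinks if less information is available at the look. The mismatch is worth correcting before the look. Trial status reports 60 randomisations as of July 2014, so at that point the look had not been reached.

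**What to change.** Replace the fixed pair with a Lan-DeMets O'Brien-Fleming spending function evaluated at the information actually available at the look, and state how information is measured for the time-to-event primary analysis. Derive both limits together: about 0.011 and 0.047 if information is 65%. Do not change the interim limit alone, since keeping 0.048 would take overall alpha to about 0.051-0.052. The cost is a sentence in the protocol and a slightly stricter final threshold; no extra patients are needed.

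Alternatively, keep 0.005 as a deliberately conservative fixed interim limit, drop the O'Brien-Fleming attribution, and recompute the final limit (about 0.049 at 65%). This leaves the lower chance of early stopping in place, but as a declared choice.

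Moving the look to 77 randomised patients to preserve the printed numbers is not a good remedy. It again treats randomised patients as information, would give less than 50% if analysed at that moment, and brings the look forward.

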#### Subsidiary studies

In addition to the primary and secondary endpoints above, the trial will generate data to inform further sub-studies. These will relate to the trial questions which are not directly linked to the pleurodesis efficacy of talc, and the details of their analysis are beyond the scope of this protocol. Sub-studies will include the following:Examining whether the measurement of pleural elastance can be used to predict lung entrapment (pleural manometry).Examining whether serum levels of NT-pro BNP at baseline are related to pleurodesis success.Health economic analysis: the perspective adopted in the economic analysis will be that of the English National Health Service and Social Services. As a result we will collect information on the following resource use items:Intervention costs: This will entail collecting information on talc, consumables and staff time. This information will be obtained by reviewing hospital records. Should a significant between-group difference in the rates of IPC blockage and drain removal occur, these will also be included in the intervention cost analysis.Follow-up costs: This will entail collecting information on patients’ use of hospital resources after randomisation. Information collected will include inpatient stays, outpatient services, use of emergency departments and ambulance costs. Information on inpatient stays will be obtained by reviewing the administrative care records in each of the participating centres.

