### Study setting and design

The IPC-PLUS study is a non-commercial, patient-blind, multicentre, randomised controlled trial of a medicinal product. Patients will be recruited from multiple centres within the United Kingdom. The trial is supported by the appropriate local and regional cancer networks.

Clinical care, drain insertion and imaging will be provided by local medical professionals at the patients’ base hospitals or appropriate satellite centres. Further care will be provided by ward and specialist nurses in these centres, who will also be available for telephone support. Routine drainage of pleural fluid will take place in the community and at follow-up visits. All drainages up to the 28-day post-randomisation visit will be performed by appropriately trained medical staff such as district nurses, lung cancer specialist nurses or research nurses. After this, drainages may be performed by anyone who has been appropriately trained (except the patient themselves).

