SA06	• New sites added: Northampton, Ayr, Cambridge, Aintree and Hull
	• Change of inclusion criteria to require World Health Organisation (WHO) performance of two or better to be eligible, three if score will decrease to two after drainage.
	• Allow patients with previous pleurodesis as long as longer than 56 days before trial entry
	• Relax follow-up visits by allowing day 42 and 56 to be carried out over the telephone
	• Allow carers or relatives to perform chest drains after the day 28 post-randomisation visit
	• Extend recruitment period to May 2015
	• Relaxation of manometry recordings from every 100 ml to every 100 to 200 ml
	• Updated membership of the Trial Steering Committee

The following CRFs will be used during the trial: enrolment, baseline assessment, IPC insertion, day 10 assessment and randomisation, follow-up, telephone follow-up, thoracic ultrasound appearances, health resource utilisation and withdrawal.

In addition to the above, patient data will also be collected via a daily patient VAS score booklet and a daily IPC drainage volume booklet.

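### Blockage and drain-removal costs are counted only if the arms differ significantly, and the listed follow-up costs do not name community drainage

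*Protocol article*

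**What the plan says.** Cost-effectiveness of talc plus IPC against IPC alone is the last of the secondary research questions under Study questions. The costing is described under Subsidiary studies, where "the perspective adopted in the economic analysis will be that of the English National Health Service and Social Services".

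Two groups of cost follow.

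- Intervention costs: "This will entail collecting information on talc, consumables and staff time", and "This information will be obtained by reviewing hospital records". The article then adds a conditional component: "Should a significant between-group difference in the rates of IPC blockage and drain removal occur, these will also be included" in the intervention cost analysis. It does not state the test, the significance level, or whether blockage and removal are judged separately or must both differ.
- Follow-up costs: "This will entail collecting information on patients’ use of hospital resources after randomisation". The items named are inpatient stays, outpatient services, emergency departments and ambulance costs.

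On where drainage happens, Study setting and design says "Routine drainage of pleural fluid will take place in the community and at follow-up visits". Community drainage sets a starting frequency of three times a week and a minimum of twice a week. It has trained professionals drain up to and including the day 28 visit, and allows family or carers to do so afterwards. Each drainage volume is recorded, and Data collection lists "a daily IPC drainage volume booklet" together with a health resource utilisation form.

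**The concern.** The conditional sentence is a stated rule, so it can be judged as it stands. It uses a significance test to decide whether a cost that was actually incurred is counted. The quantity of interest in a cost-effectiveness analysis is the difference in mean cost, with its uncertainty. If the test is not significant, the rule in effect sets the difference in that component to zero and removes its uncertainty. If the test is significant, the component enters with an observed difference that had to be large to pass. Neither result is a fair estimate of the cost difference.

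Blockage matters for this comparison. The section on blockage of drains asks for an adequate flush after the sclerosant is given, so the investigators foresaw the problem. If talc blocked more drains, leaving out a non-significant excess would make talc look cheaper than it is.

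The second, smaller matter is scope. The stated perspective is the health service and social services, but the named follow-up items are all hospital or ambulance items. Community drainage is a recurring cost in both arms, and it should fall if talc brings pleurodesis forward. The Background itself links IPC cost to drainage kits and to how long the catheter is in use.

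**Working it through.** **Inputs.** From Sample size and power calculation: 60% against 85%, 90% power, 5% significance, 5% loss to follow-up, 154 patients (77 per arm). From the Statistical analysis plan section: two-sided tests. The article gives no blockage or removal rates, so those below are assumptions. The gate's significance level is not stated, so 5% is assumed.

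**Step 1: reproduce the planned size.** With d = 0.25 and a mean proportion of 0.725,

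n = [1.96·√(2·0.725·0.275) + 1.2816·√(0.60·0.40 + 0.85·0.15)]² / 0.25² = (1.238 + 0.777)² / 0.0625 ≈ 64.9, so 65 per arm.

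With continuity correction, n′ = (n/4)·[1 + √(1 + 4/(n·d))]² = (64.9/4)·(1 + 1.116)² ≈ 72.7, so 73. Then 73/0.95 = 76.8, so 77 per arm and 154 in total. The stated figure is reproduced. Without the correction the result is 69 per arm, or 138.

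**Step 2: chance that the gate opens.** For rates p₁ and p₂ with mean p̄ and n = 77 per arm,

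power = Φ{[|p₂ − p₁|·√n − 1.96·√(2p̄(1 − p̄))] / √(p₁(1 − p₁) + p₂(1 − p₂))}.

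- Blockage 5% v 10%: (0.05·8.775 − 1.96·0.3725)/0.3708 = (0.439 − 0.730)/0.371 = −0.786, so 22%.
- Removal 30% v 40%: (0.878 − 1.322)/0.671 = −0.663, so 25%.
- Removal 60% v 85%: (2.194 − 1.238)/0.606 = 1.577, so 94%.

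| Event | Assumed rates | Chance of significance |
|---|---|---|
| Blockage | 2% v 5% | 17% |
| Blockage | 5% v 10% | 22% |
| Blockage | 10% v 20% | 41% |
| Blockage | 5% v 15% | 54% |
| Blockage | 5% v 20% | 81% |
| Removal | 30% v 40% | 25% |
| Removal | 30% v 45% | 49% |
| Removal | 40% v 60% | 70% |
| Removal | 60% v 85% | 94% |

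With 73 evaluable per arm the three worked cases become 21%, 24% and 93%. For 80% power, 5% v 10% would need 435 per arm and 30% v 40% would need 356.

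If the rule means that both rates must differ, the chance cannot exceed the smaller of the two. It would be at most 22% with blockage at 5% v 10%, even if removal passed easily.

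**Step 3: what passing requires.** Five per cent of 77 is about 4 patients. Against 4 blockages, 11 in the other arm give z = (7/77)/√(2·0.0974·0.9026/77) = 1.90, which fails. Twelve give z = (8/77)/√(2·0.1039·0.8961/77) = 2.11, which passes. At that base rate the cost enters only once the observed rate is three times as high.

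**Step 4: scope.** The four follow-up items under Subsidiary studies also appear under Face-to-face appointments as examples of contacts to be recorded (admissions, outpatient visits, emergency visits, ambulance use). Neither list names community nursing or home drainage kits. Both lists are introduced as inclusive, so they are not strictly exhaustive.

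**The case against.** Several points on the other side have force.

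- The gate covers the intervention cost analysis only. Inpatient, outpatient and emergency use are costed without condition, and removals are done by appointment, so blockages and removals handled in hospital may already be counted there. This stands. It reduces the likely bias and means that the fix must avoid double counting.
- If removal tracks the planned pleurodesis effect, that half of the gate would usually open. This also stands, provided the two rates are judged separately.
- The article defers the details of the sub-study analyses. That weakens the scope point, but it does not excuse an inclusion rule that the article itself states.
- Consumables and staff time could be read to cover home kits and nursing, and the contents of the resource utilisation form are not shown. This stands as well: it cannot be said that community drainage will go uncosted. What can be said is that it is not named, and that the stated source, hospital records, would not normally hold district nurse visits.

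A reader might go further and infer that the cost-effectiveness question will be answered without its main cost drivers. The document does not support that. It gives no unit costs and no ranking of costs, and blockage and removal are conditional rather than excluded.

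A reader might also multiply the planned 25-point difference by the last five weeks and by two to three drainages a week (0.25·5·2 = 2.5; 0.25·5·3 = 3.75) and read the result as saved nurse visits. That assumes that drainage stops at success, which no section says, that the gap holds to week 10, and that nobody dies. It also ignores that carers may drain after day 28, which covers that whole window.

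**Conclusion.** The significance condition is a poor costing rule and should go. Under illustrative rates, moderate differences would usually miss significance with 77 per arm: about 22% power for blockage at 5% v 10%, and about 25% for removal at 30% v 40%. A difference in removal as large as the planned pleurodesis effect would usually pass, at about 94%. These figures assume a two-sided 5% test by normal approximation, without adjustment for the minimisation variables.

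The incremental cost could be biased. The size cannot be computed, because the article gives neither event rates nor unit costs, and part of the cost may already sit in hospital use. The conclusion is that the cost result could be biased, not that it will be wrong.

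The absence of community drainage from the listed items is a secondary point. The list fits poorly with the stated perspective, but it may reflect condensation or a broad meaning of staff time and consumables. The matter is confined to the cost-effectiveness sub-study. The primary endpoint, its analysis and the sample size are unaffected.

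**What to change.** Delete the significance condition. Cost every blockage and every drain removal in both arms whatever the p-value, and let the uncertainty show in the interval around the incremental cost. State that an event already captured as outpatient or inpatient use is not costed a second time.

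Add community drainage to the listed costs: a drainage kit for each drainage recorded in the booklets, and nurse time only where a nurse attended. Because carers may drain after day 28, who performed each drainage must be identified. The article describes the booklet as a record of volumes and does not say that it records this. If neither the booklet nor the resource utilisation form holds it, one extra field is needed, or a stated assumption with a sensitivity range for drainages already done.

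The cost is a change of wording, unit costs for kits and nurse visits, a rule against double counting, and possibly that one field. Drainage counts can already be derived from the recorded volumes.
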